### Safety considerations

As part of the contact email sent to interested participants, a link is provided to a PDF containing information on always-available support services for crisis situations. In case of concerns or questions, participants may contact the research team at any time via email or by phone during designated office hours, or reach out to their group therapist or group facilitator during group or individual sessions, or through the messaging function within the Primary Data Collection Tool. Within the group sessions in both programmes, concepts for following supportive treatments are discussed, but such services are not directly provided or arranged for the participants.

The Primary Data Collection Tool facilitates the documentation of safety-relevant data that could potentially lead to an early termination of the study (see the section below for more information). An adverse event (AE) is defined as any undesirable experience that occurs to a participant during the trial and that may affect the intervention itself, the exclusion criteria or the participant’s ability to continue participating in the study. These events can be reported by participants or group therapists, group facilitators, or research team members at any time point during the study in the Data Collection Tool. Participants are regularly reminded of this option in the group sessions. Serious adverse events (SAEs), i.e. breach of trust in the study members, acute worsening of depressive symptoms, hospitalisation, self-harm, suicide attempts or suicide, will be documented in the case report form and reported to the main study site (MSB).

The study will also be monitored by an Independent Data and Safety Monitoring Board (IDSMB) specifically chosen to include a geriatrician, a geropsychiatric, a statistician and a clinical psychologist, ensuring the utmost competence and vigilance. The IDSMB will meet via videoconference before, during and after the trial to review its progress and provide an independent evaluation of the safety of the participating patients (especially in the event of SAEs) and adherence to the protocol (data integrity and the validity of the clinical trial). If necessary, the frequency of the web conferences can be increased. The study will only continue if it is deemed safe by the IDSMB, which can also provide the sponsor with information and make recommendations.

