
In light of the aforementioned research gaps, the implementation of a video-based group psychotherapeutic programme targeting older adults with depression and comorbid anxiety constitutes a pioneering intervention – particularly in light of the high clinical care demand. In terms of the VISION-AGE programmes’ content, the rationale focuses on improving adaptive forms of self- and developmental regulation strategies. These are outlined as follows: (1) positive self-perceptions of ageing, (2) life review (strengthening reminiscence), (3) life management (training SOC-strategies) and (4) life planning. This approach is embedded within a therapeutic concept that traverses the three biographic ‘time corridors’ past - present - future. The primary therapeutic methods originate from LRT, but were enriched by CBT and therapeutic techniques of Positive Psychology (PP).

In order to develop an efficient psychotherapeutic programme, it is crucial to examine how patients interpret, memorise and realise the psychological input received over the course of a treatment. In this regard, qualitative methodologies provide insight into the individual patient’s perspective on the therapeutic change [35]. Therefore, the present study employs a mixed-methods approach, triangulating quantitative and qualitative methodologies.

In the context of this innovative therapeutic concept, and considering that the manual for the control group represents an adapted extension of an already proven helpful concept [36], the potential benefits and study objectives are the reduction of symptoms of depression, anxiety as well as the increase of psychological well-being and concepts of self- and developmental regulation. No health risks are expected to be associated with data collection or the programme, as all participants will receive support. As participants in both conditions will be dealing with personal issues and each other, temporary mood deterioration may occur. However, given the qualifications, training and supervision of our group therapists (leading the intervention group) and group facilitators (leading the control group), no significant long-term harms or deterioration are expected, even after the programme ends.

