### Intervention-group VISION-AGE

VISION-AGE is a standardised, age-sensitive group psychotherapy programme carried out via video conference by trained psychotherapists. The treatment manual was tested in the psychotherapeutic university outpatient clinic of the MSB Medical School Berlin during a three-year pilot phase and was refined in an iterative process based on clinical experiences and patient feedback. There was no evidence of any negative therapy effects. The manual focuses on promoting self- and developmental regulation strategies and thereby addresses the three biographical ‘time corridors’ past - present - future. Well-established LRT methods are enriched by CBT and PP techniques. In addition to the 20 group sessions, four individual sessions (each 45 min long) are intended to reinforce the therapeutic alliance and deepen the content of the group sessions. The initial upstream module focuses on reflecting upon and modifying existing images and experiences of ageing, as well as addressing ageism, in order to build the motivation necessary for change (Module 1 Positive self-perceptions of ageing), followed by Module 2 Life-review, Module 3 Life-management and Module 4 Life-planning. An accompanying handbook is sent to participants prior to the intervention, providing preparatory tasks related to specific sessions of the manual (e.g. collecting photos for the LRT sessions or a gratitude exercise for the Life-management sessions). For an overview of the therapeutic manual’s contents and the postulated mechanisms of action, see the supplemental material.

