### Termination criterion

If a participant withdraws their informed consent during the study, as termination criteria, all data collected up to that point will be removed from the analysis dataset, with the deletion duly documented.In addition, participation in the study may be terminated early under the following circumstances:If a participant does not wish to continue participating or cannot be reached, or fails to attend required study visits (drop-out);If a participant starts an ambulant psychotherapy between the assessment points T0 and T7;If a participant changes their psychoactive medication, continued study participation will be reviewed on a case-by-case basis in consultation with the participant and PI;If health problems arise that are not related to the study content, but may hinder focus-targeted or regular study participation, continued study participation will be reviewed on a case-by-case basis in consultation with the participant and PI. This includes new or worsening physical complaints (e.g. a fall followed by hospitalization), serious events (e.g. the unexpected death of a family member) or psychological complaints (e.g. acute grief – except for depression and anxiety, which are dealt with under point [f]);If any SAE occur, decisions regarding continued participation will always be made by the PI in consultation with the IDSMB, to ensure the participant’s well-being and the appropriateness of their involvement. The jointly made decision will be transparently communicated to the participant;If a participant passes away during the study period;If the PI or study sponsor decides to discontinue participation for specific reasons.

In the event of early termination, the termination criteria are recorded on an individual basis, specifying the corresponding time point and category.

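### The adverse event definition requires a possible effect on the intervention, eligibility or participation, so non-acute mood deterioration, a harm the protocol foresees, can be neither an AE nor an SAE

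*Protocol article*

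**What the plan says.** All references are to the protocol article.

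- **Safety considerations, AE definition.** An AE is "any undesirable experience that occurs to a participant during the trial and that may affect the intervention itself, the exclusion criteria". A third alternative completes the condition, namely a possible effect on whether the person can stay in the trial. The sentence before the definition introduces the record as "safety-relevant data that could potentially lead to an early termination of the study".
- **Safety considerations, SAE list.** Besides breach of trust, the listed events are: "acute worsening of depressive symptoms, hospitalisation, self-harm, suicide attempts or suicide, will be documented in the case report form". This list does not carry the condition attached to AEs.
- **Background, last paragraph before Objectives.** Because participants in both conditions deal with personal issues and with each other, "temporary mood deterioration may occur". The same paragraph adds that "no significant long-term harms or deterioration are expected, even after the programme ends".
- **Termination criterion.** The item on health problems unrelated to the study content covers psychological complaints, "except for depression and anxiety, which are dealt with under point [f".
- **Primary outcomes and Table 3.** The PHQ-9 is taken at T1 to T7, on the same schedule in both arms, as the primary outcome.

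**The concern.** An adverse event record should first say what happened to participants, and only then what it meant for the trial. Here the two are joined by an 'and': an experience counts only if it may also affect the intervention, eligibility or continued participation. A participant who feels worse after a session, without acute worsening, and who keeps attending and remains eligible need not be recorded. That is close to the kind of event the Background says may occur.

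What is at stake is the completeness of the AE record. If it is used to describe harm in the two arms, it will lean towards harm that disrupts participation, and a low count would owe something to the definition. The condition also asks whoever reports to judge a possible effect on the trial, and some of those people know the arm.

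**Working it through.** There is no stated figure to reproduce and no arithmetic behind the main point. The check sets the rules side by side.

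**1. Form of the definition.** Write U for an undesirable experience during the trial, and I, E and C for a possible effect on the intervention, the exclusion criteria and the ability to continue. The text says AE = U and (I or E or C). U alone is not enough.

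**2. Sort mood deterioration by the rules as written.**

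| Kind of deterioration | Rule that applies | Recorded as |
|---|---|---|
| Acute worsening of depressive symptoms | SAE list | SAE |
| Worsening that may reach very severe depressive or anxiety symptoms | Exclusion criteria [a] and [b], hence E | AE |
| Worsening that may affect the intervention or attendance | I or C | AE |
| Non-acute worsening, participant still eligible and attending, no apparent effect on the intervention | none | neither |

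The fourth row can hold the temporary deterioration that the Background foresees.

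**3. Does the Termination criterion section close the gap?** It sends depression and anxiety to point [f]. The list letters are lost in the text at hand. Counting consent withdrawal as [a], then drop-out, new psychotherapy, medication change and health problems as [b] to [e], point [f] is the SAE item. That leads back to the SAE list, which names acute worsening of depressive symptoms and does not name anxiety. No lower tier appears for non-acute worsening.

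**4. Does the PHQ-9 close the gap?** Only in part.

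- The Assessment section places T2 after group session 4, T3 after session 10, T4 after session 15 and T5 after session 19. Sessions are weekly, so the intervals are about 10 − 4 = 6, 15 − 10 = 5 and 19 − 15 = 4 weeks. The six-week interval from T2 to T3 contains the whole life-review module. T7 comes six months after the programme. A dip that begins and ends within an interval can be missed.
- Nothing in the article turns a PHQ-9 rise into an AE entry. Under Data acquisition, data management and data archiving, research team members in general see only whether a questionnaire was completed, not its content.

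**5. Who applies the condition?** Under Safety considerations, participants, group therapists, group facilitators and research team members can report. The therapists and facilitators know the arm because they deliver it. They also differ in training between arms: psychotherapists in the intervention group, certified senior citizen assistants in the control group (Recruitment of group therapists and group facilitators). A judgement on whether an event may affect the trial could therefore be made differently in the two arms. The article does not show that it would be.

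**The case against.** The strongest reply is that the gap is narrow and the harm is measured elsewhere. Much of this stands.

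- **Worse mood is not left out in general.** A reader might infer that mood deterioration goes uncounted altogether. The document does not support this: acute worsening is an SAE with no further condition, and worsening that may reach an exclusion criterion or affect attendance is an AE.
- **The condition is elastic.** It says that the event may affect the intervention, and in a fixed group of four one participant's low mood could do so. The Discussion itself notes that individuals can weigh heavily on group dynamics. A generous reporter would record more than the literal minimum. This shrinks the gap, but it also makes the count depend on who reports.
- **The protocol foresees the harm; it does not predict it.** The Background says that it may occur, that it is temporary, and that no significant long-term harm is expected.
- **Mood is assessed systematically.** The PHQ-9 and health-related changes are collected at T1 to T7, the MADRS by blinded assessors at T1, T6 and T7, and the qualitative interviews deliberately include intervention participants who deteriorated. The trial would not be blind to lasting deterioration; it is the AE record alone that may fall short.
- **No head count follows.** It is tempting to turn the assumed effect sizes (d = 0.75 within, d = 0.45 between) into a number of participants who worsen by T6. That would need a pre-post correlation and a cut-off that the article does not give. It would also count people whom the PHQ-9 already captures at T6, not unrecorded events.
- **The pilot statement is separate.** "There was no evidence of any negative therapy effects" describes the earlier pilot phase. Nothing shows that it was obtained under this definition. Nor does the article confine the monitoring board to the AE log.

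**Conclusion.** The point holds in a limited form. As written, non-acute mood deterioration that does not threaten eligibility or participation can be neither an AE nor an SAE, although the Background foresees temporary mood deterioration in both arms. The AE record alone may understate this harm, and the condition that decides inclusion is judged partly by people who know the arm.

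The size cannot be stated: the article gives no rate of such events, and none can be derived from its figures. The conclusion assumes that the definition is applied as worded and that the full protocol does not replace it with a broader one. It does not bear on the primary analysis. This is a worthwhile correction to a stated rule, not a flaw that undermines the trial.

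**What to change.** 1. In Safety considerations, end the AE definition after the words 'during the trial', so that any undesirable experience counts.
2. Record the present condition (possible effect on the intervention, the exclusion criteria or continued participation) as a separate yes/no field on the AE form. The count under the current definition then remains available as a subset.
3. Report by arm the number of participants with PHQ-9 deterioration from T1, with the cut-off fixed beforehand, from the scores already collected at T1 to T7. This table may sit in the analysis plan; it supplements the AE record.

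This changes only what is recorded and reported. The cost is one amended sentence, one extra field and one descriptive table. The downside is more minor events to log.

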### Control group

The active CG is a non-clinical group discussion programme designed to provide social support and stimulation through group discussions in a supportive, non-judgemental environment. During the first half of each session, participants discuss personal, everyday issues from the previous week, followed by a discussion of stimulating, neutral topics such as hobbies, cooking, or animal companionship. Group facilitators encourage engagement and socialisation among group members, similar to the type of support participants might receive in a community support group at a senior citizens’ centre. The manual is based on one used in a previous study [36], where it showed a small positive effect on depression and anxiety in older patients, and has been adapted and expanded for the present study. The CG programme will be delivered by senior assistants, as the work requirements align with their usual work tasks and no clinical skills are necessary. To achieve the same therapeutic dosage as the IG, the time allocated to group therapy sessions is identical to that of the IG. In terms of individual contact, participants will receive four five-minute friendly digital meetings with their group moderator, as well as four additional 40-minute audio features offering stimulating content related to the preceding sessions (e.g., about the benefits of having an animal companion). See the supplemental material for an overview of the group discussion manual, including the discussion topics.

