In the primary data system, all members of the research team can view, within each participant’s history, whether the participant attended a group session (without any specific role assignment, only the session number, no content), a digital visit, or completed a questionnaire (attendance only, without access to the content). Thus, information on participant adherence is available without unblinding the research team. Due to the program’s regular group sessions, the group therapists and facilitators have a clear overview of participants’ adherence, which is discussed routinely during supervision meetings. The Primary Data Collection Tool enables automated reminder emails to be sent to participants, and in cases of dropout, telephone contact may be initiated to inquire about continued interest in participation.

Once the intervention phase is completed, following the last participant’s assessment, the technical support team by XPERTyme GmbH will generate two datasets from the study`s data capture before closing it: one with the source data and one with the relevant pseudonymized study data, suitable for statistical analysis. Both datasets will be protected with a checksum and archived separately from each other at the Medical School Berlin (MSB). Both the source data and the raw dataset will be retained for a minimum of 10 years in accordance with regulatory requirements. In addition, a member of the research team will generate a de-identified dataset from the pseudonymized data. After the retention period has expired, all records containing personal information will be securely deleted or destroyed, except for the de-identified dataset, as they no longer contain any personal reference. Access to identifiable information is strictly limited and may only be granted to auditors, or ethics committees for oversight purposes.

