**Further exploratory measures**								
• Working Alliance (WAI-SR)					x			
• Group Cohesion (FEPiG)					x			
• Programme Satisfaction (ZUF-8)							x	x
• Pre-programme: Assessment of individual therapeutic goals (across five categories); Post-programme: Goal attainment scale		x					x	x
• Assessment of medical resource utilization (self-developed questionnaire)		x					x	x
• Health-related life quality (EQ-5D-5L)		x					x	x
• Acceptance of video technology (TUQ)			x	x	x	x	x	x
• Assessment of health-related changes (self-developed questionnaire)		x	x	x	x	x	x	x
**Safety relevant data**	Notification is possible at anytime.							

Note. **T0** = Enrolment, afterward Allocation, **T1** = Baseline assessment, **T2–T5** = intermediate assessment, **T6** = post-treatment assessment, **T7** = FU assessment

The data collection will be conducted on seven time points to assess the short- and medium-term effects of the VISION-AGE-intervention, and will be identical for both the IG and CG. The assessment points include:

A baseline assessment prior to the start of the intervention;Following completion of the first module (Positive self-perceptions of ageing, i.e., group session 4);Following the second module (Life-review, i.e., group session 10);Following the third module (Life-management, i.e., group session 15);Following the fourth module (Life-planning, i.e., group session 19);Two weeks after the end of the programme (i.e., group session 20); and Six months post-programme (FU).

To encourage continued participation, the study participants receive greeting cards, which include memories of the group sessions, once they have completed all six assessment points.

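### Harms are captured by open notification with no scheduled enquiry, and acute worsening of depression is tied to no scale, so ascertainment may differ between arms

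*Protocol article*

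**What the plan says.** All references are to the protocol article.

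- **Route of capture.** Safety considerations says of adverse events: "These events can be reported by participants or group therapists, group facilitators, or research team members at any time point during the study". It adds: "Participants are regularly reminded of this option in the group sessions". In Table 3 (Assessment), where the outcome, mediator and exploratory measures have marked time points, the safety row reads only: "Notification is possible at anytime".
- **Serious adverse events.** These are listed as "breach of trust in the study members, acute worsening of depressive symptoms, hospitalisation, self-harm, suicide attempts or suicide". They are to be documented in the case report form and reported to the main study site. No scale, threshold or time frame is given for the worsening category.
- **Who leads the groups.** The intervention is a "group psychotherapy programme carried out via video conference by trained psychotherapists". The control programme is led by senior assistants, and the Control group section says that "no clinical skills are necessary".
- **Who sees scores.** Under Data acquisition, data management and data archiving, research team members in general see whether a participant "completed a questionnaire (attendance only, without access to the content". The principal investigator has full access. Under Randomization and blinding, so do team members responsible for supervision. Leaders may see the data of their own group's participants.
- **What is measured identically in both arms.** The PHQ-9 is taken at T1 to T7, the MADRS at T1, T6 and T7, and a self-developed questionnaire on health-related changes at T1 to T7.

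**The concern.** Under open notification an event enters the record only if somebody notices it and decides to file it. For a hospitalisation that may matter little. For acute worsening of depressive symptoms it matters more, because the category has no stated criterion and someone must judge whether it has occurred. Group leaders are one of the main observers. They know the allocation, and they differ by arm in clinical training and in the time they spend alone with a participant.

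Two things are at stake. First, a between-arm comparison of harms could reflect how events were found as well as how often they happened. Second, the reports feed decisions. Under Termination criterion, any serious adverse event leads to a decision on continued participation by the principal investigator with the safety board. Under Safety considerations, the trial continues only if the board deems it safe. Unequal detection could therefore also lead to unequal discontinuation by arm. As the plan is written, a participant's PHQ-9 score could rise sharply without any described step that turns the rise into a safety entry.

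**Working it through.** The plan states no adverse event rate and no detection figure, so there is no stated safety figure to reproduce. The check is of contact time, of the routes by which an event could surface, and of how far unequal detection could move a comparison.

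**1. Contact time with the group leader** (inputs: Intervention; Intervention-group VISION-AGE; Control group)

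| | Intervention | Control | Comparison |
|---|---|---|---|
| Group sessions | 20 x 100 = 2000 min | 20 x 100 = 2000 min | identical |
| One-to-one, live | 4 x 45 = 180 min | 4 x 5 = 20 min | 180/20 = 9 |
| Total live | 2180 min | 2020 min | 2020/2180 = 0.93 |
| Total live without breaks (20 x 90) | 1980 min | 1820 min | 1820/1980 = 0.92 |

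The control arm also receives 4 x 40 = 160 minutes of audio features, but these involve no live contact. The arms thus differ ninefold in private live time and by only 7 to 8% in total live time.

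**2. Routes by which worsening could be recorded**

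| Route | Same in both arms? | Limit as described |
|---|---|---|
| Participant's own report | Yes | Voluntary; reminders are given in the group sessions, so none is described for the six months to T7 |
| Group leader | No: training and one-to-one time differ | No criterion for worsening |
| Blinded visits | Yes | T1, T6 and T7 only |
| Supervision from session videos | Yes | Group sessions and qualitative interviews are named as recorded; individual meetings are not |
| PHQ-9 and MADRS scores | Yes | No stated link from a score to a safety entry |
| Health-changes questionnaire | Yes | Described content is medication changes and new diagnoses; the form itself is not shown |
| Principal investigator's data access | Yes | Described for data integrity, consent and protocol compliance |

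Between T1 and T6 the leader is the only staff member scheduled to see participants live.

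**3. How far unequal detection could matter (all rates assumed)**

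The expected number of recorded events per arm is n x true risk x detection probability. The plan gives n = 125 per arm. With equal true risk in both arms, the spurious ratio of intervention to control is the ratio of the detection probabilities, whatever the risk.

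| Assumed detection, intervention / control | Events at 10% true risk | Events at 5% true risk | Ratio |
|---|---|---|---|
| 90% / 90% | 11.3 / 11.3 | 5.6 / 5.6 | 1.0 |
| 90% / 75% | 11.3 / 9.4 | 5.6 / 4.7 | 1.2 |
| 90% / 60% | 11.3 / 7.5 | 5.6 / 3.8 | 1.5 |
| 90% / 45% | 11.3 / 5.6 | 5.6 / 2.8 | 2.0 |

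Worked example: 125 x 0.10 x 0.90 = 11.25 and 125 x 0.10 x 0.60 = 7.5; 11.25/7.5 = 1.5. If the two detection rates are exchanged, the ratio is 7.5/11.25 = 0.67. Nothing in the document fixes the rates or says which arm has the higher one.

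**The case against.** The strongest case on the other side has five parts.

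- **Leaders are not the only route.** Participants and research team members may report, participants are reminded in both arms, and they can also reach the team by email, telephone or platform message. This stands.
- **The ninefold figure covers a small part of the contact.** Group time is identical, and the first half of each control session is given to personal matters of the past week, where worsening could surface. This stands: the difference lies in clinical qualification and private contact, not in overall exposure.
- **Arm-neutral checks exist.** There are blinded visits at T1, T6 and T7, video-based supervision, the principal investigator's full data access and an independent safety board. They reduce the risk. None is described as a systematic enquiry about harms, and the board can assess only what reaches it.
- **Serious events must be documented and reported.** That duty applies once an event is known; the text does not say how it becomes known.
- **An article may leave forms and thresholds to the full protocol.** This is fair for a numerical threshold and for the content of the health-changes questionnaire, so the absence of such questions cannot be asserted. But Table 3 does state how safety data are obtained, and that stated method is open notification.

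A reader might infer that harms will be under-detected in the control arm, or that no valid comparison of harms will be possible. The documents support neither. No detection rate is given, several routes are the same in both arms, and deterioration on the PHQ-9 and MADRS can be compared symmetrically.

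**Conclusion.** The point holds as a risk of differential ascertainment, not as a demonstrated bias. Three facts in the protocol article carry it: safety data are captured by open notification with no scheduled enquiry, acute worsening of depressive symptoms is tied to no instrument, and one main group of reporters differs by arm in clinical qualification and in one-to-one live time (180 against 20 minutes, with equal group time).

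The size and direction of any bias cannot be computed from the document. The ratios of 1.0 to 2.0 shown above follow entirely from assumed detection rates and only indicate sensitivity. The conclusion also assumes that the health-changes questionnaire does not already ask about the serious event categories; if it does, the first part of the fix is already met. The change is worth making because it is cheap and makes the comparison of harms rest on the same procedure in both arms.

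**What to change.** 1. **Ask directly.** Put the serious event categories from Safety considerations as direct questions, worded the same in both arms, into the health-changes questionnaire at each assessment after baseline (T2 to T7), if they are not already there. Keep spontaneous notification as a supplement, since it also covers participants who stop completing questionnaires.
2. **Tie worsening to the scales.** The sponsor and the safety board pre-specify one criterion on the PHQ-9 (T2 to T7) and the MADRS (T6, T7). The platform applies it automatically and without regard to arm, and lists the cases for the principal investigator and the board. The threshold is theirs to set.
3. **Separate the two sources in the analysis.** Base the between-arm comparison of harms on the systematically collected events, and report spontaneous notifications separately.

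Trial status gives a start date of 1 December 2025. If recruitment has begun, the criterion should be fixed before anyone examines the data by arm; it can then be applied to scores already collected, whereas new questions count only from their introduction.

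Cost: a few questionnaire items, one automatic rule and one listing, with more events to review. Visits and sample size do not change.

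### Anxiety is routed to the SAE rule, but the SAE list has no anxiety item, so acutely worsening anxiety does not trigger that rule

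*Protocol article*

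**What the plan says.** Two adjacent sections of the protocol article bear on this.

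**Safety considerations.** An adverse event (AE) is "any undesirable experience that occurs to a participant during the trial and that may affect the intervention itself, the exclusion criteria" or the person's ability to continue. SAEs are defined as "Serious adverse events (SAEs), i.e. breach of trust in the study members, acute worsening of depressive symptoms, hospitalisation, self-harm, suicide attempts or suicide", and these "will be documented in the case report form and reported to the main study site (MSB"). The IDSMB meets before, during and after the trial to "provide an independent evaluation of the safety of the participating patients (especially in the event of SAEs") and of adherence to the protocol.

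**Termination criterion.** This section lists the circumstances in which participation may end early. One item opens "If health problems arise that are not related to the study content" and provides for individual review with the participant and the PI. Its examples include psychological complaints such as acute grief, "except for depression and anxiety, which are dealt with under point [f"]. The next item reads "If any SAE occur, decisions regarding continued participation will always be made by the PI in consultation with the IDSMB". The last is a general power: "If the PI or study sponsor decides to discontinue participation for specific reasons".

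**The concern.** The pointer shows that the authors meant depression and anxiety to be handled together, through the stronger of the two routes. That works only if worsening of either one counts as an SAE. The SAE list delivers this for depression and not for anxiety. Read as written, a participant with acute grief gets an individual review with the PI. A participant whose anxiety worsens acutely is excluded from that review and does not meet the trigger of the rule meant to replace it.

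Anxiety is not a side issue in this trial. The population is older adults with depression, with or without anxiety; anxiety reduction is hypothesis H2a; and very severe anxiety is an exclusion criterion. The Background section accepts that mood may deteriorate temporarily in either arm. What is at stake is consistent safety handling, not the efficacy comparison.

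**Working it through.** No figure in the plan is in question, so the check sets the two sections side by side.

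**Step 1: which item is [f]?** The item letters are not visible in the text at hand, so the match has to be inferred. There are two possible counts.

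- *Consent withdrawal counted as [a]:* [b] drop-out, [c] outside psychotherapy, [d] medication change, [e] unrelated health problems, [f] SAE, [g] death, [h] PI or sponsor decision. The SAE rule is item 6 of 8.
- *Count started after the consent sentence:* [a] drop-out, [b] outside psychotherapy, [c] medication change, [d] unrelated health problems, [e] SAE, [f] death, [g] PI or sponsor decision. Point [f] is then the participant's death, which cannot be the place where depression and anxiety are dealt with.

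The other lettered lists do not fit either. Inclusion [f] concerns language skills and exclusion [f] concerns terminal physical illness. Only the first count gives the pointer a meaning, and it makes [f] the SAE rule.

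**Step 2: what triggers the SAE rule?** The list is introduced by *i.e.*, whereas the Termination criterion section uses *e.g.* where it gives examples. The natural reading is a closed definition. Its entries are:

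1. breach of trust
2. acute depressive worsening
3. hospitalisation
4. self-harm
5. suicide attempt
6. suicide

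One entry of six concerns depressive symptoms; none concerns anxiety.

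**Step 3: do the two rules meet?**

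- *Depression, acute worsening:* removed from the unrelated-health-problems item, sent to [f], and listed as an SAE. The route is complete.
- *Anxiety, acute worsening with hospitalisation, self-harm or a suicide attempt:* an SAE through those entries. The route is complete.
- *Anxiety, acute worsening without any of these:* removed from the unrelated-health-problems item, sent to [f], and not listed as an SAE. The route is broken.

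**Step 4: what still catches the third case?**

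- Participants, therapists, facilitators and research staff can report it as an AE at any time. The AE definition refers to the exclusion criteria, so anxiety that reaches the very severe level named there is covered.
- The PI has access to all study data (Data acquisition section).
- The IDSMB's safety review is not confined to SAEs.
- The general discretionary item lets the PI or sponsor end participation.

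None of these requires SAE documentation, SAE reporting to the main site, or consultation with the IDSMB about the individual participant. The Termination criterion section attaches no participation decision to a non-serious AE as such.

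**The case against.** The strongest reply is that the pointer is itself an instruction. If anxiety is to be dealt with under the SAE rule, a reader who takes both sections together will bring it to the PI and the IDSMB whether or not the list names it. It can be added that the identity of [f] is inferred, that a condensed article may leave SAE detail to the full protocol, and that the fallback routes cover most of the ground.

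Part of this stands. The intention is clear, the fallbacks are real, and the remaining gap is small. But the rule at [f] is activated by an SAE, and the printed definition of an SAE leaves anxiety out. Two printed rules disagree, which is different from detail left to another document. If the other count were right, the pointer would lead to the item on death, and anxiety would still not be covered.

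A reader might also infer that the assessment schedule makes the gap more serious for anxiety than for depression, since the PHQ-9 is taken at T1 to T7 and the anxiety scale (GAS) only at T1, T6 and T7. The protocol does not support that. It nowhere gives the PHQ-9 scores at T2 to T5 a safety role or makes a score a trigger for action. The PHQ-9 is there as the primary outcome.

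**Conclusion.** The point holds as a minor inconsistency between two safety rules. Acutely worsening anxiety without hospitalisation, self-harm or a suicide attempt is taken out of the case-by-case review and does not meet the SAE definition to which it is sent. The loss is limited to SAE documentation, SAE reporting to the main site, and the mandatory IDSMB consultation.

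This rests on two readings: that [f] is the SAE rule, inferred from order and sense, and that the SAE list is closed, as its wording indicates.

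It would go too far to infer that worsening anxiety is left without any safety handling. AE reporting, PI access to the data, general IDSMB review and the discretionary item all remain. The protocol gives no rate of worsening anxiety, so no number of affected participants can be stated. Sample size, power and the primary analysis are untouched.

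**What to change.** Add acute worsening of anxiety symptoms to the SAE list in Safety considerations, parallel to the depression entry. In Termination criterion, check that the pointer names the SAE rule; naming the rule in words instead of by letter would remove any doubt.

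Giving anxiety its own termination item and correcting the pointer would also resolve the conflict. Extending the list is preferable because it delivers the routing that the section already states.

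The cost is a few words and a few more SAE reports for the PI and the IDSMB. No analysis or assessment changes.
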